### Randomization and intervention

After written informed consent is obtained, patients eligible for the study, will be randomized intraoperatively into two groups:Group A: Skin closure with non-coated suture material poliglecaprone 25 (Monocryl®, Ethicon GmbH, Norderstedt, Germany)Group B: Skin closure with triclosan-coated poliglecaprone 25 (Monocryl® Plus Ethicon GmbH, Norderstedt, Germany)

The randomization sequence is performed with sealed opaque envelopes. The patients are block randomized with equal block sizes of 20 items per block (allocation of patients per block is 1:1). The randomization list generation is computer-based using the *Random Allocations Software Version 1.0.0* (Freeware) by M. Saghaei, MD.

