#### Secondary outcome measures

Wound dehiscence and re-operation rate due to wound dehiscence within 30 days, all-cause 30-day mortality, and length of hospital stayOccurrence of any SSI within one year after implantation of a foreign body

Furthermore, we will evaluate potential risk factors for poor wound healing, such as gender, age, BMI, ASA classification, diabetes mellitus, antidiabetic medication, present immunosuppression, wound class according to CDC criteria, operative time, amount of blood loss, length, and orientation of incision [3, 10].

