### Statistics/sample size calculation

The sample size is estimated on the basis of a two-sided chi^2^ test for equality of the proportions of SSI occurrence within 30 days in the treatment and control groups (null hypothesis). Based on evidence in the literature, an infection rate of 12% is assumed for the control group and it is expected that the use of antibacterial sutures will reduce the SSI rate to 4% in the treatment group [11, 12].

Thus, a treatment effect of − 0.08 is assumed (i.e., an absolute risk reduction of 8 percentage points). Furthermore, the significance level of the test is set to 5% and a power of 80% is desired. To determine the sample size, we generate 10,000 synthetic data sets for a range of potential sample sizes using the above-mentioned assumptions for the SSI rates in both study groups. That is, we generate realizations of independent binomial random variables with probabilities of SSI occurrence p_T_ = 0.04 and p_C_ = 0.12, respectively. With each bi-variate data set, the two-sided chi^2^ test is performed at level α = 0.05.

Then, the power associated with a particular sample size n results in the H_0_-rejection rate across the 10,000 tests performed with data sets of size n. Hence, we obtain the power of the test as a function of the sample size and can identify the best value of n corresponding to a power of at least 80%. All computations are performed in the statistical software environment R (R Core Team, 2018, *R: A Language and Environment for Statistical Computing*. R Foundation for Statistical Computing, Vienna, Austria).

We find that, given a test level of α = 0.05, a total of 344 patients are needed to show that the SSI rates are different with a power of at least 80%. Furthermore, accounting for an expected drop-out rate of 5%, we obtain the number of *N* = 364 study participants to be recruited, that is, 182 patients for each study group.

All analyses will be performed after termination of the main part of the trial, that is, after the last 30-day follow-up visit has taken place.

The full analysis set (FAS) will include all study participants who were randomized and for whom data from at least one follow-up visit are available.

The per protocol set (PPS) will include all study participants in the FAS for whom the intervention was completed as planned and for whom complete data on all endpoints

are available.

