All statistical analyses will be performed on the FAS according to the intention-to-treat principle. In addition, all analyses will be repeated using the PPS instead to assess the robustness of the findings.

The primary analysis investigates whether the SSI rate (within 30 days) among patients receiving antibacterial sutures is different from the rate in the control group, using a two-sided chi^2^ test for equality of proportions (null hypothesis) at significance level α = 0.05.

Besides the test result, the estimated SSI rates in the two groups and the estimated SSI rate difference will be reported with their 95% confidence intervals, the latter describing the precision of the estimates.

In addition to the primary analysis, we will assess the difference between the treatment and control groups when controlling for general risk factors for poor wound healing such as age and BMI of a patient or length and orientation of the incision. This will be achieved by evaluating the odds ratio obtained from estimating a multiple logistic regression model for the binary endpoint SSI (within 30 days) with explanatory factor treatment and adjusted for risk factors for poor wound healing. To further explore potential benefits of using antibacterial sutures, the differences between the treatment and control groups regarding the following secondary endpoints will be assessed:Wound dehiscence within 30 days (yes/no)Re-operation due to wound dehiscence within 30 days (yes/no)Death within 30 days (yes/no)Length of hospital stay (days)

The first three secondary outcomes will be analyzed estimating simple and multiple logistic regression models with explanatory factor treatment and, in the multiple case, adjusted for general risk factors for poor wound healing. The secondary endpoint length of hospital stay will be assessed using Poisson regression models instead.

For the subgroup of patients whose surgery involves the implantation of a foreign body, an additional long-term follow-up visit will take place one year after surgery. Once these data are collected, a final secondary analysis will be done for this subgroup of patients evaluating their SSI risk (within one year).

For all secondary analyses, parameter estimates and odds ratios will be reported together with 95% confidence intervals. If *p* values are reported, they will be interpreted as continuous measures of evidence against the associated null hypotheses.

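### Simple and multiple logistic models are fixed for dehiscence, re-operation and 30-day death whatever the event count; at rates near 1% they often cannot yield the promised odds ratio

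*Protocol article*

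**What the plan says.** The section Statistics/sample size calculation of the protocol article sets out these analyses.

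- **SSI, adjusted.** The treatment odds ratio comes from "estimating a multiple logistic regression model for the binary endpoint SSI (within 30 days) with explanatory factor treatment", adjusted for risk factors for poor wound healing. Four are named as examples: age, BMI, incision length and incision orientation.
- **Dehiscence, re-operation due to dehiscence, death (all within 30 days).** "The first three secondary outcomes will be analyzed estimating simple and multiple logistic regression models with explanatory factor treatment". The multiple versions adjust for the same general class of risk factors.
- **Reporting.** All secondary analyses are to give estimates and odds ratios with 95% confidence intervals. Any p values are read as graded evidence, not as decisions.

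The section Secondary outcome measures has a longer list of potential risk factors, "such as gender, age, BMI, ASA classification, diabetes mellitus, antidiabetic medication, present immunosuppression, wound class according to CDC criteria, operative time", followed by blood loss and the length and orientation of the incision. That makes twelve.

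The article does not name the estimator and does not tie the number of covariates to the number of events. It gives no expected rate for dehiscence, re-operation or death.

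**The concern.** Logistic regression needs events in both arms to give a finite treatment odds ratio, and more events for each covariate added. The article fixes the model type and the reported quantity for three endpoints that may be rare. Emergency surgery is excluded, and re-operation due to dehiscence can occur only in patients who have dehiscence.

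If an arm has no events, or a covariate category perfectly predicts the outcome, standard fitting diverges. The analyst must then choose a replacement after seeing the data. Death and re-operation bear on safety, so this is an awkward place to improvise. The adjusted SSI odds ratio will be read beside the primary result, so it also matters whether that model is overloaded.

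**Working it through.** **Inputs from the article.** The design is based on a "two-sided chi^2^ test for equality of the proportions of SSI occurrence within 30 days"; "the significance level of the test is set to 5% and a power of 80% is desired"; "an infection rate of 12% is assumed for the control group"; the coated suture is expected to "reduce the SSI rate to 4% in the treatment group"; "allocation of patients per block is 1:1". Evaluable total 344 (172 per arm); 364 after 5% drop-out.

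**Assumed.** Rates of 0.5 to 3% for dehiscence, re-operation and death, equal in both arms; covariate distributions and effects in the simulations.

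**1. The plan's own figure.** Exact enumeration of the two binomials with the uncorrected chi-square test gives power 80.35% at 344 and 79.82% at 340, so 344 reproduces. 344 / 0.95 = 362.1, which becomes 363, or 364 for equal groups.

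**2. Expected SSIs.** 172 × 0.12 + 172 × 0.04 = 20.6 + 6.9 = 27.5.

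- Treatment plus the four named factors: 5 parameters, 27.5 / 5 = 5.5 events per parameter.
- Treatment plus all twelve, with the four wound classes as 3 parameters: 1 + 11 + 3 = 15 parameters, 27.5 / 15 = 1.8.

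**3. Adjusted SSI model (1,000 simulated trials of 344).**

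- Unadjusted: mean log odds ratio −1.25 against a true marginal value of −1.19, about 6% too large.
- Four factors: −1.29 against a true conditional value of −1.22, about 5% too large (about 8% against the marginal value). Treatment was estimable in 99.9% of trials; coverage was 97%.
- Twelve factors (15 parameters): −1.38 against −1.22, about 13% too large. Coverage was 96%. Some coefficient diverged in 34% of trials, but the treatment coefficient in only 0.1%. A Firth-penalised fit gave −1.22.

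**4. Rarer endpoints, no covariates.** With rate p in each arm, the chance that at least one arm has no events is 1 − (1 − (1 − p)^172)². For p = 0.01: 0.99^172 = 0.178, and 1 − 0.822² = 0.32. This depends only on p and the arm size.

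**5. Rarer endpoints with covariates.** Share of trials in which some coefficient is not estimable, by simulation:

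| Assumed rate | Expected events in 344 | An arm with zero events | Four factors | Twelve factors |
|---|---|---|---|---|
| 0.5% | 1.7 | 67% | 79% | 100% |
| 1% | 3.4 | 32% | 47% | 99.8% |
| 2% | 6.9 | 6% | 14% | 96% |
| 3% | 10.3 | 1% | 4% | 88% |

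The last two columns move with the covariate assumptions. A second check of the four-factor model gave about 50, 19 and 4% at 1, 2 and 3%. A third, with independent covariates that had no effect, gave 39, 10 and 1%.

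These columns count divergence of any coefficient. The treatment coefficient alone failed less often: 31, 6 and 1% with four factors at 1, 2 and 3% (as in the unadjusted model), and 45, 10 and 1.5% with twelve.

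**The case against.** The strongest reply has four parts.

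- **Estimator and detail.** The article never says maximum likelihood, and a Firth fit is also a logistic model. The covariate list, estimator and sparse-data fallback commonly belong in an analysis plan, which is not shown. This stands as far as it goes: their absence is not the point. The point is that the article commits to adjusted odds ratios for all three endpoints whatever the event count.
- **The twelve-factor model.** A reader might infer that all twelve factors enter every model, and so that the SSI odds ratio is seriously biased or cannot be estimated. The article does not say this. The longer list serves an evaluation of risk factors, while the analysis text names four as examples. With those four, adjustment adds almost nothing to the small-sample bias already in the unadjusted fit. A reader might also infer a built-in tilt towards the coated suture. The distortion only enlarges an effect that exists: with equal 8% rates in both arms, the simulated mean log odds ratio was 0.00 with no covariates or four, and −0.01 with sixteen.
- **Rates.** Rarity is assumed. Dehiscence is not defined as fascial and may not be rare. This stands, and is why a range is shown. At 3% with four factors the models can mostly be fitted.
- **Status.** These analyses are secondary and non-confirmatory, and unadjusted models are already planned beside the adjusted ones. The first part stands. The second helps only in part: at 1% the unadjusted model itself has an empty arm in about a third of trials.

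**Conclusion.** The point holds for the sparse secondary endpoints. If death, re-operation or dehiscence occurs at about 1% or less, standard logistic regression has no finite treatment odds ratio in about a third to two thirds of trials, even unadjusted. With the four named factors at 1%, some coefficient fails in roughly 45–50% of trials; with all twelve, in nearly all trials at 1–2%. At 3% with four factors the problem is small.

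The zero-event figures rest only on the assumed rate and 172 per arm. The covariate figures also rest on assumed covariate distributions and effects.

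For SSI, the adjusted analysis is acceptable with the four named factors. Exaggeration of about 10–14% on the log scale arises only if the model approaches twelve factors and a true effect exists. The documents do not support a claim that the primary result is affected: that is an unadjusted chi-square test. This is a worthwhile, inexpensive improvement to exploratory analyses, not a flaw in the trial's main conclusion.

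**What to change.** For death, re-operation due to dehiscence and any other endpoint with few events, replace the multiple models with:

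- event counts per arm;
- the risk difference with a Newcombe or Miettinen-Nurminen 95% confidence interval, which remains defined when an arm has no events;
- a treatment-only Firth-penalised odds ratio, or a Fisher exact p value.

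State before the data are seen what counts as few events, so that dehiscence is handled by rule if it proves more common.

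For SSI, limit the adjusted model to age, BMI, incision length and incision orientation, or use a Firth-penalised fit if more factors are entered.

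The cost is wording in the protocol or analysis plan, and less covariate adjustment in exploratory analyses. Sample size, data collection and the primary test do not change. The article reports 280 of 364 patients enrolled and defers all analyses until the last 30-day visit, so at that stage the change could still precede analysis.

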## Methods/design

This single-center prospective randomized controlled trial (RCT) is conducted at the Department of General-, Visceral- and Thoracic Surgery and the Department of Obstetrics and Gynecology at the AGAPLESION Diakonie Hospital Rotenburg (Wuemme) gGmbH, Germany. It is designed as a double-blind parallel-group superiority trial.

All patients planned for elective open general/colorectal or gynecological abdominal surgery will be consecutively informed about the study. Informed consent will be signed by each participating patient and a member of the study team at least 24 h before elective surgery. A flow diagram for this trial is shown in Fig. 1.

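### Length of hospital stay is assigned to Poisson regression with 95% confidence intervals and no provision for overdispersion, so the interval is probably too narrow

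*Protocol article*

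**What the plan says.** The relevant text is in the protocol article, Statistics/sample size calculation. Four secondary endpoints are to be compared between groups. The three yes/no endpoints (wound dehiscence, re-operation for dehiscence, death, each within 30 days) get simple and multiple logistic regression. For the fourth, stay in days, the text says: "The secondary endpoint length of hospital stay will be assessed using Poisson regression models instead".

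On reporting it says: "For all secondary analyses, parameter estimates and odds ratios will be reported together with 95% confidence intervals". Of any p values it says that "they will be interpreted as continuous measures of evidence against the associated null hypotheses".

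No dispersion parameter, robust variance or alternative model is named. No mean, standard deviation or distribution of stay appears anywhere in the article.

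Two other places bear on how variable stay will be. Methods/design describes recruitment across specialties: "All patients planned for elective open general/colorectal or gynecological abdominal surgery will be consecutively informed about the study". Secondary outcome measures gives the candidate risk factors, beginning "such as gender, age, BMI, ASA classification, diabetes mellitus, antidiabetic medication, present immunosuppression, wound class according to CDC criteria" and continuing with operative time, blood loss, and length and orientation of the incision. Specialty or type of operation is not named, although the list is open-ended.

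**The concern.** Poisson regression estimates the ratio of mean stays, and that estimate does not depend on the variance assumption. Its default standard error does, because it is computed as if variance equalled mean. When patients differ in their expected stay for reasons that the model does not contain, the variance is the mean plus the variance of those expected stays, which is larger.

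This trial has several such reasons: two surgical departments, wound classes from clean to dirty, and a minority with infection, dehiscence or re-operation. Covariates can absorb part of the spread. They cannot properly absorb the part due to complications, which arise after randomization.

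What is at stake is the stated precision of one secondary result. Shortening hospital stay is a secondary objective in the Background section, so its interval will be read. An interval that is too narrow could present chance variation as a difference in stay between the sutures.

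**Working it through.** **The plan's own figure.** There is none for length of stay. The only related figure is the sample size, and it reproduces: exact power of the uncorrected two-sided chi-square test at 172 per arm (344 in total) with rates of 12% and 4% is 80.3%. Nothing below bears on it.

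**Formula.** Let φ be the variance/mean ratio of stay that remains after the model's covariates. The default Poisson standard error is too small by a factor √φ. A nominal two-sided 5% test then rejects a true null with probability 2 × [1 − Φ(1.96/√φ)], and the coverage of the nominal 95% interval is 1 minus that. Sample size does not enter, so a larger trial does not help. For φ = 5: √5 = 2.24, 1.96/2.24 = 0.88, error 38.1%, coverage 61.9%.

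| φ (assumed) | SE too small by | Error at nominal 5% | Coverage of nominal 95% CI |
|---|---|---|---|
| 1.0 | 1.00 | 5.0% | 95.0% |
| 1.2 | 1.10 | 7.4% | 92.6% |
| 1.5 | 1.22 | 11.0% | 89.0% |
| 2 | 1.41 | 16.6% | 83.4% |
| 3 | 1.73 | 25.8% | 74.2% |
| 5 | 2.24 | 38.1% | 61.9% |

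**Which φ is plausible?** Two sources can be sketched from the trial's own features. All lengths of stay used here are assumptions.

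*Infection alone.* The protocol says "an infection rate of 12% is assumed for the control group" and expects that coated sutures "will reduce the SSI rate to 4% in the treatment group". Pooled, p = (12% + 4%)/2 = 8%. If an infection adds d days to a base stay b, and stay is otherwise exactly Poisson, then mean = b + p·d and variance = mean + p(1 − p)·d², with p(1 − p) = 0.0736.
- b = 10, d = 5: mean 10.4, variance 10.4 + 1.84 = 12.24, φ = 1.18, coverage 93%.
- b = 8, d = 10: mean 8.8, variance 8.8 + 7.36 = 16.16, φ = 1.84, coverage 85%.
- b = 6, d = 14: mean 7.12, variance 7.12 + 14.43 = 21.55, φ = 3.03, coverage 74%.

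*Specialty mix alone.* Take a 50:50 mix of two specialties, each exactly Poisson, with means m₁ and m₂. The variance is the overall mean plus [(m₂ − m₁)/2]².
- Means 7 and 10: 8.5 + 2.25 = 10.75, φ = 1.26, coverage 92%.
- Means 5 and 10: 7.5 + 6.25 = 13.75, φ = 1.83, coverage 85%.
- Means 5 and 12: 8.5 + 12.25 = 20.75, φ = 2.44, coverage 79%.

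Each sketch isolates one source; independent sources add to the variance. The upper end of the range, φ = 5, corresponds to an SD of about 7 days at a mean of 10 (49/10 = 4.9). At the other end, an SD of about 3.2 days or less at a mean of 10 gives φ of 1 or below, and the default interval is not too narrow.

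**Check by simulation.** 10,000 two-arm trials with 182 per arm, no true difference, assumed mean stay 10 days, gamma-Poisson data:

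| SD (days) | φ | Rejection, default Poisson SE | Rejection, robust SE |
|---|---|---|---|
| 3.16 | 1.0 | 5.0% | 5.2% |
| 5 | 2.5 | 22.6% | 5.5% |
| 7 | 4.9 | 37.3% | 4.6% |
| 10 | 10 | 53.7% | 5.2% |

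The default standard errors behave as the formula predicts. The same Poisson model with a robust variance holds its level throughout.

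**The case against.** The strongest objection is that the article names a model family and not a variance estimator. Poisson regression with sandwich or scaled standard errors is still Poisson regression, the simulation shows that it gives valid results, and the choice could sit in an analysis plan that is not shown. This stands as a limit on the point: the protocol has not excluded a correct analysis. It does not remove the point, because the protocol does commit to a model whose default interval is probably too narrow here. Settling this within that commitment takes one sentence.

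Second, the ratio that matters is conditional on covariates. The wording suggests that adjusted models are meant for stay too, and wound class, operative time and incision length would take up some of the difference between specialties. This also stands. The specialty sketch applies directly to an unadjusted model and overstates the problem for an adjusted one. The excess from complications remains in both.

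Third, stay is an exploratory secondary endpoint, and p values are to be read without a threshold. So the error rates above do not describe a decision that the plan will take. The coverage figures need no threshold, however: a 95% interval that covers less often is misleading in itself, and a p value from too small a standard error overstates the evidence. Repeating the analysis in the per protocol set would carry the same error.

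A reader might also infer that the stay analysis could produce a false cost-saving claim, or that in-hospital deaths would count as favourable short stays. The article supports neither. The abstract's Discussion ties cost saving to a lower infection rate, not to the stay analysis. Nothing says how stay is recorded for patients who die, a patient who dies may have had a long stay, and 30-day death is analysed separately.

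**Conclusion.** The point holds as a should-fix. The protocol assigns length of stay to Poisson regression with 95% confidence intervals and makes no provision for overdispersion, which is likely in this case mix. If default standard errors are used, coverage of the nominal 95% interval is about 93% at a residual variance/mean ratio of 1.2 and about 62% at a ratio of 5. At a ratio near 1 there is nothing to correct. These figures rest on assumed ratios, because the article has no data on stay.

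A reader might conclude that the Poisson assumption certainly fails and that the results will be far too optimistic. The documents do not support that certainty: the loss of coverage may be slight or severe, and robust standard errors are not ruled out. The primary chi-square test, its significance level and the sample size of 364 are untouched.

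**What to change.** State one method for length of stay before the analysis. Either of these would do:

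- negative binomial regression with a log link; or
- the log-link Poisson model already named, with quasi-Poisson or sandwich standard errors.

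In either case, report the ratio of mean stays (coated to uncoated) with its 95% confidence interval, from the unadjusted and the adjusted model. The second option leaves the protocol's sentence intact and only adds the variance estimator.

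The cost is one sentence and a different function call or option. It needs no new data and does not change the sample size. The interval widens by about √φ, that is 1.10-fold at a ratio of 1.2 and 2.24-fold at 5. If the ratio proves to be near 1, the result barely changes.
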